### Fidelity, reach, and feasibility of the intervention

We will register the number of educational booklets and book chapters distributed out of all caretakers in the intervention arm, if more booklets, and chapters than enrolled caretakers have been distributed, we will immediately try to understand to whom and why has it been given as it may be a contamination. If a chapter or video was missed in an IPT pick-up, we will register the occurrence and the reason, and provide two chapters at the next visit. We will record the SMS delivered and the videos and SMS delivered, since August 2021. At the end of the follow-up, we will recruit caretakers from the intervention arm balancing those who completed IPT and those who interrupted or discontinued it and conduct semi-structured interviews. We will explore whether the materials were read, how the content was perceived, how much the materials influenced their daily provision of IPT to the child under their care, the reactions of the children and whether it influenced caretakers, which content worked and why, and what may be missing or unhelpful. We will also explore the effect that the COVID-19 pandemic had on the provision of IPT to the child and if anyone at home developed COVID-19.

### Oversight and monitoring

Daily conduction of the trial is overseen by the principal investigator and the study coordinator. The steering committee is composed of the principal investigator and two co-investigators who meet monthly to discuss progress. The Ethics Committee requests annual reports and can conduct audits at any time. Annual progress reports are submitted to the funder and sponsor.

### Provisions for post-trial care

There is no anticipated harm and compensation for trial participation.

### Limitations and alternative approaches

Contamination may occur if caretakers of different arms share the booklet. Although this is possible, we will recruit participants from a large geographical area of 700,000 population to reduce the clustering of caretakers who know each other. This will be explored with caretakers at the end of the intervention. We will conceal group allocation but cannot blind the intervention to those delivering it or receiving it.

Considering the non-monetary nature of the incentive, we do not expect adverse effects of incentives such as fraudulent practices or the perverse incentive effect in which the incentive provokes the opposite of the intended behavior.

## Discussion

### Adaptations to the COVID-19 pandemic

We report adaptations using the CONSERVE SPIRIT Checklist (Additional file 1: Appendix 2) [38]. On 18 March 2021, approximately 3 months after starting recruitment and because of extenuating circumstances imposed by the COVID-19 pandemic, we stopped in-person recruitment of new participants and the delivery of one of the three components of the intervention, the children’s storybook and continued delivering the SMS to the participants enrolled (*n* = 39). Attendance at primary care facilities was restricted to essential services to reduce the risk of SARS-CoV-2 transmission.

We modified the study protocol and requested an amendment to the UPCH IRB to (1) enroll study participants over the phone after a brief in-person introduction (< 5-min interaction in open air) of the study to reduce contact frequency and duration at health facilities, (2) to deliver the three components of the interventions through WhatsApp (instead of one through SMS and two in physical books), and (3) to include a question in the participant questionnaire, to learn if the participant or somebody at the participant’s house had had a COVID-19 diagnosis, the outcome, and the approximate date of the diagnosis. We developed a 5-min video of the educational booklet with communication specialists and developed 2-min narrated and musicalized videos of the 24 chapters of the children’s storybook so that the three components of the intervention could be delivered by phone. We restarted recruitment in August 2021.

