### Study participants

Eligible participants will be caretakers of children who are (1) < 5 years old, (2) a contact of a TB patient, and (3) have an isoniazid preventive treatment (IPT) prescription from the TB physician. We will exclude caretakers not interested in participating in the study, those who do not have a mobile phone or, since August 2020, a smartphone with internet access using WhatsApp.

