### Data management and analysis

Data will be imported into Stata V16. We will compare the proportion of children who completed IPT in both groups with statistical tests for small groups in an intention-to-treat approach, including all enrolled participants in the denominators. We will also compare the median number of weekly IPT pick-ups. We will compare the characteristics of caretakers, index cases, and children of the intervention and control arm. Missing data will be reported in descriptive tables. Medians and interquartile ranges will be calculated for continuous variables and proportions for categorical variables. Despite randomization, there may be confounding present regarding the probability of completing IPT. Potential confounders include the index case characteristics (sex, age, smear status), child characteristics (sex, age, kinship to the index case), caretaker’s characteristics (sex, age, kinship to the child, and to the index case, occupation, and education) the socio-economic status of the family and the health facility. To determine an unconfounded estimate of the effect of the intervention in the proportion of children who completed IPT, we will test models with a multivariate backward regression analysis. A saturated model with variables associated with IPT completion in our preliminary findings (smear status and treatment outcome of the index case, kinship and TST result of the child [14] and other variables associated (*p* < 0.1) with the outcome in the bivariate analysis will be tested against a model with variables with the weakest associations eliminated one by one. We will analyze the timing of the drop-outs (caretakers not coming back to pick up IPT) with Cox regression and the factors associated to that timing with a multivariate Cox regression analysis. We will report the proportion of enrolled to those eligible overall for the intervention group as well as per health facility, and we will report the full cascade of IPT (evaluation, prescription, initiation, completion) for the intervention and control facilities during the study period. As the data for the outcomes are routinely collected, we will follow the REporting of Studies Conducted using the Observational Routinely Collected Health Data (RECORD) statement to report the study findings [37].

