## Trial status

Protocol version 2.0, July 2020. Recruitment began in December 2019. Recruitment was temporarily stopped in March 2020, re-started in August 2020, and is anticipated to end in December 2022. Follow-up will continue until June 2023.

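### The intervention, the eligibility rule and clinic access changed around the COVID-19 pause, but the adjusted model names no period term and the dates of the pause conflict

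*Protocol article*

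**What the plan says.** Two sets of changes are described, at two different times.

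- **At the stop.** The section on adaptations to the pandemic says that in-person recruitment and the storybook were halted while SMS went on for the 39 participants already enrolled. It adds: "Attendance at primary care facilities was restricted to essential services to reduce the risk of SARS-CoV-2 transmission".
- **At the restart.** The same section describes an amendment "to deliver the three components of the interventions through WhatsApp (instead of one through SMS and two in physical books". Study participants adds the criterion "since August 2020, a smartphone with internet access using WhatsApp"; before that, a mobile phone was enough.

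The main analysis is stated in Data management and analysis: "We will compare the proportion of children who completed IPT in both groups with statistical tests for small groups", by intention to treat with every enrolled child in the denominator. The adjusted analysis lists index case, child, caretaker, socio-economic and facility variables. It then builds a model from earlier findings and bivariate associations at p < 0.1, reduced by backward elimination. Neither the list nor the procedure names period, date of IPT start or version of the intervention.

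The dates disagree. The adaptations section has "On 18 March 2021, approximately 3 months after starting recruitment" and "We restarted recruitment in August 2021", and the fidelity section has "We will record the SMS delivered and the videos and SMS delivered, since August 2021". Trial status has "Recruitment was temporarily stopped in March 2020, re-started in August 2020, and is anticipated to end in December 2022". Study participants, the rationale for the intervention and the educational material section also use August 2020.

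**The concern.** The primary outcomes count pick-ups at the clinic: at least 22 of 24, or all 24. Three missed weeks fail both definitions, since 24 − 3 = 21. A period of restricted attendance therefore acts directly on the endpoint, and period is likely to be a strong predictor of completion.

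Two things follow. First, if one arm has more children from before the stop than the other, part of the difference between arms is a difference between periods. Second, even with the same mix in both arms, the result is an average over print plus SMS and all-WhatsApp delivery, and over caretakers with any mobile phone and those with a smartphone. The 39 also lost a component during follow-up.

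The planned COVID-19 information does not fill the gap. It consists of a questionnaire item and end-of-study interviews with intervention caretakers, whereas control data are described as coming from treatment cards.

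**Working it through.** **Inputs.** Planned enrolment is 100 intervention and 200 control children, in 10 and 20 clusters of 10; ICC 0.38; planned completion 70% against 30% (Power calculations). There were 39 participants at the stop (adaptations section). SMS goes only to the intervention arm (SMS reminders section). Completion by period and the number of controls enrolled before the stop are not given, so the ranges below are assumptions. The plan has no figure of its own on this point to reproduce.

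**1. Share before the stop.** If all 39 are intervention children, which the SMS rule makes probable, the share is 39/100 = 39%, and the control share is unknown. If the 39 were instead both arms split 1:2, the shares would be 13/100 and 26/200, 13% each.

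**2. Exposure of the 39.** Take the 2020 dates and assume IPT starts at enrolment. A child enrolled on 1 December 2019 had 108 days, or 15.4 weeks, before 18 March 2020. That leaves 24 − 15.4 = 8.6 weeks after the stop. Every earlier enrolee therefore had at least about 8 of 24 pick-up weeks under restricted access.

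**3. Bias of the pooled difference.** Bias = (s_I − s_C) × d, where s_I and s_C are the shares before the stop in each arm and d is the difference in completion between periods.

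| Period difference d | Equal shares | 39% vs 19.5% | 39% vs 0% |
|---|---|---|---|
| 10 points | 0 | 2.0 | 3.9 |
| 20 points | 0 | 3.9 | 7.8 |
| 30 points | 0 | 5.9 | 11.7 |

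The sign depends on which period has the lower completion and which arm has the larger early share.

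**4. Type I error.** Simulation: 30 clusters of 10, ICC 0.38, 30% completion after the restart, a 20-point period difference, no true effect, cluster-level t-test at two-sided 5%, 4,000 runs per scenario.

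| Shares before the stop | Unadjusted | With period term |
|---|---|---|
| 13% vs 13% | 4.6% | 4.9% |
| 39% vs 39% | 5.0% | 5.0% |
| 26% vs 6.5% | 6.2% | 5.5% |
| 39% vs 19.5% | 6.6% | 5.1% |
| 39% vs 0% | 9.8% | 5.3% |

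With the period term the simulated bias was about zero in every scenario, and the term did no harm when shares were equal.

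**5. Precision of an effect by period.** Assume the same mix in both arms (39 and 78 children early, 61 and 122 late) and completion of 70% and 30%.

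- Early: 3.9 per cluster, design effect 1 + 2.9 × 0.38 = 2.10, effective sizes 18.6 and 37.1. SE = √(0.21/18.6 + 0.21/37.1) = 0.130, so the 95% interval is about ±26 points.
- Late: 6.1 per cluster, design effect 1 + 5.1 × 0.38 = 2.94, effective sizes 20.8 and 41.5. SE = 0.123, about ±24 points.

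**6. Dates.** From 1 December 2019, 18 March 2020 is 108/30.4 = 3.6 months at most, which fits the stated interval of about three months. 18 March 2021 is 473/30.4 = 15.6 months, which does not. Protocol version 2.0 of July 2020 also fits a restart in August 2020.

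**The case against.** The strongest reply is that no imbalance is shown. Facilities were randomized concurrently in groups matched on burden, recruitment is described as one process for both arms, and its suspension is not limited to one arm. Concurrent enrolment tends to give similar shares, and then the bias is zero. This stands. A reader might infer from the 39 SMS recipients that the main comparison is confounded, or that controls were picked from cards over three years. The documents support neither: the arm split of the 39 is inferred, the control share is not given, and the cards are named as the control data source, not as a way of selecting children retrospectively.

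It may also be said that a period covariate belongs in an analysis plan that is not shown, and that the confounder list is open-ended. Silence alone would be no finding. Here, however, the article sets out both its covariates and its selection rule. Under that rule, period could enter only by passing p < 0.1 and could then be eliminated.

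A reader might further infer that the conflicting dates cause bias or put children under the wrong version. They do not: no stated analysis uses the date, delivery of materials is recorded, and the article's other dates point to 2020.

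Finally, pooling by intention to treat across a documented adaptation is legitimate. That stands too, and nothing here argues against it. Restricting controls to matching IPT-start windows would change the sampling and could clash with the all-enrolled denominator, so it is not proposed.

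**Conclusion.** The point holds as a gap in the stated adjustment, not as demonstrated confounding. With equal early shares there is no bias. In the extreme of 39% against 0%, and for an assumed period difference of 10 to 30 points, the bias is about 4 to 12 points in an unknown direction, against a planned difference of 40 points. Type I error at a 20-point period difference ranges from about 5% to 9.8%. These figures rest on assumed completion differences and on reading all 39 as intervention children.

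Independently of any imbalance, the pooled estimate averages two delivery versions and two eligible populations, and the report should say so. The date conflict is a separate reporting error. It matters because one date has to define the period.

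**What to change.** 1. Keep all enrolled children in the analysis.
2. Define period by date of IPT start, before the stop or after the restart, from the pick-up dates already collected in both arms. State a rule for any start date that falls between the two.
3. Force period into the adjusted model and keep it out of backward elimination.
4. Report enrolment by arm and period, so that a reader can see whether the shares differ.
5. Give the effect by period as a descriptive secondary analysis, stating its low precision.
6. Reconcile the dates in the adaptations and fidelity sections with those in Study participants, the rationale, the educational material section and Trial status.

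The cost is one degree of freedom, a little more analysis work and a date correction. No new data and no change to sampling are needed.

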## Trial status

Protocol version 2.0, July 2020. Recruitment began in December 2019. Recruitment was temporarily stopped in March 2020, re-started in August 2020, and is anticipated to end in December 2022. Follow-up will continue until June 2023.

## Dissemination policy

We will disseminate our results as peer-reviewed manuscripts, oral presentations or abstracts. Technical briefs will be prepared to disseminate relevant findings to the National TB Program and participant health facility.

## Data Availability

All data generated or analyzed during this study will be made available on request upon completion of the study.

## Abbreviations

TB: Tuberculosis
BCG: Bacille Calmette-Guérin
TPT: TB preventive therapy
SMS: Short message services
IPT: Isoniazid preventive therapy
LTBI: Latent TB infection
COVID-19: Coronavirus disease of 2019
LMIC: Low- or middle-income countries
HIC: High-income countries
DOPT: Directly observed preventive treatment
SPIRIT: Standard Protocol Items: Recommendations for Interventional Trials
VMT: Villa Maria del Triunfo
SJM: San Juan de Miraflores
ESN-PCT: Estrategia Sanitaria Nacional de Prevención y Control de la Tuberculosis
CDC: Centers for Disease Control and Prevention
SOC: Standard of care
TST: TB preventive therapy
SARS-CoV-2: Severe acute respiratory syndrome coronavirus 2
SIDISI: Sistema Descentralizado de Información y Seguimiento a la Investigación
